### Hypotheses

The experimental group will have a lower incidence and prevalence of PUs than the control group at the end of the implementation of the protocol.The care staff in the experimental group will have more PU knowledge than the care staff in the control group at the 8^th^ week, and at the end of the implementation of the protocol.The care staff in the experimental group will have higher-level PU prevention skills than the care staff in the control group at the 8^th^ week, and at the end of the implementation of the protocol.

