### Study procedures

The four trained RAs, who are registered nurses and will be blind to the group allocation, will collect the data. Each RA will be responsible for collecting the data for two nursing homes. The following data will be collected from both the experimental and control groups (Table 1). Immediately before (T0) the lecture, at the 8^th^ week (T1), and at the end of the implementation (T2) of the protocol (at the 16^th^ week of the implementation of the protocol), the staff participants will be assessed on their knowledge on preventing pressure ulcers in the presence of the RAs. Before the commencement of the skill training (T0), at the 8^th^ week (T1), and at the end (T2) of the implementation of the protocol (T3), the RAs will conduct an individual assessment of the staff participants’ skills on turning, positioning, transferring, lifting, and the use of preventive materials, while they are performing daily care for residents.

**Table 1 Tab1:** Data collection

Study outcomes	Before the lecture	Before the skill training	Immediately before commencement of protocol implementation	8^th^ week after the protocol	At the end of the protocol
Knowledge	✓			✓	✓
Skills		✓		✓	✓
Prevalence	✓		✓	✓	✓
Incidence “-------------------------------the whole period					

In assessing the incidence of PUs, the RAs will inspect the skin of each resident two times a week to detect the first PUs (on residents without PUs) and new PUs (on residents already suffering from PUs), starting from before the intensive training course to the end of the implementation of the protocol. The size, location, and stage of PUs will be assessed when they are detected. The prevalence of PUs will be evaluated by the RAs before the commencement of the intensive training course (T0), immediately before the commencement of the implementation of the protocol (T1), at the 8^th^ week (T2), and at the end (T3) of the implementation of the protocol. An inter-rater agreement of at least 90 % among four RAs will be obtained for the skill checklists and PU assessment (size, location, and stage) before the skill-training sessions.

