### Sample size

In a previous study, [9] the incidence of PUs dropped from 9.5 % to 6 % after the implementation of the programme, corresponding to an odds ratio of 0.60 [7, 8]. Based on these figures, 710 residents (355 per group) will be required for 80 % power at a significance level of 0.05. Assuming an intra-cluster correlation of 0.1 %, a total of 784 (392 per group) will be required. Based on a previous study, [8] we allow for a 20 % drop-out rate and a 90 % resident recruitment rate. We will thus need 1088 residents from eight for-profit NHs (544 residents per group). The capacity of each home should then be around 130 to 140. Based on a similar PU prevention programme for care providers [8] that increased staff knowledge and skills with a Cohen’s d of 0.95 and 1.13 respectively, a total of at least 36 care staff (18 per group) will be required to achieve 80 % power at a significance level of 0.05. Allowing for a 30 % drop-out rate and a 70 % staff recruitment rate, [8]. We estimated that at least 74 care staff (37 per group) from eight nursing homes will be required for this study.

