### Statistical analysis

IBM SPSS Statistics 22 will be used to analyse the data. An intention-to-treat analysis will be adopted. Descriptive statistics such as mean or percentage will be used to summarize PU prevention knowledge and skills, and the prevalence and incidence of PUs. A chi-square test will be performed to compare the PU prevalence and PU incidence of residents between the two groups. An independent t-test will be adopted to compare the knowledge and skills of care staff between the two groups. Generalized estimating equation (GEE) will be used to compare the two groups in terms of their performance in the knowledge and skills tests, as well as in PU status over time, and to examine the groups by the time interaction effect, adjusting for the cluster effect and possible confounders. Significance will be set at a P value of < =0.05.

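### The t-test planned for staff knowledge cannot use each person's T0 score, and the GEE uses T0 at best as a change contrast; T0 as a covariate would be more precise at almost no cost

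*Protocol article*

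**What the plan says.** The knowledge hypothesis concerns the level of knowledge at follow-up: "The care staff in the experimental group will have more PU knowledge than the care staff in the control group at the 8^th^ week", and again at the end of the protocol. Under Study procedures, at T0 (immediately before the lecture), week 8 and the end, "the staff participants will be assessed on their knowledge on preventing pressure ulcers in the presence of the RAs". Table 1 shows the same three time points.

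The Statistical analysis section names two analyses of these scores. The first is the t-test: "An independent t-test will be adopted to compare the knowledge and skills of care staff between the two groups". It names neither the visit nor whether follow-up or change scores are compared. The second is a GEE over time, used "to examine the groups by the time interaction effect, adjusting for the cluster effect and possible confounders". The confounders are not listed, and the T0 score is not named as one of them. The threshold is stated as "Significance will be set at a P value of < =0.05".

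The Sample size section relies on an earlier programme that "increased staff knowledge and skills with a Cohen’s d of 0.95 and 1.13 respectively" and concludes that "a total of at least 36 care staff (18 per group) will be required to achieve 80 % power at a significance level of 0.05". The inflation to 74 follows from "Allowing for a 30 % drop-out rate and a 70 % staff recruitment rate".

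**The concern.** The T0 knowledge score is taken before any training and is likely to predict the follow-up score. A two-sample t-test of follow-up scores ignores it. The GEE, read in the ordinary way with T0 as the first repeated response, uses it only by subtraction. Each use leaves more residual variance than a regression on T0.

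This matters because the staff comparison is small: 18 analysed per group is the stated requirement. Four homes are allocated to each arm with no stratification or matching described, so the arms may differ noticeably in starting knowledge. A t-test of follow-up scores carries part of that difference as noise. At stake is the precision of a secondary comparison.

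**Working it through.** **Inputs.** From the Sample size section: d = 0.95 for knowledge, 1.13 for skills, 18 per group, 80% power, alpha 0.05. The test is taken as two-sided, which reproduces the stated sample size. The calculation treats staff as independent, as the article's own does. The correlation rho between T0 and follow-up is an assumption; the article gives none, so a range is shown.

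**The article's own figure.** Normal approximation: n per group = 2(1.960 + 0.842)² / 0.95² = 17.4, rounded up to 18, so 36 in total. Inflation: 36 / (0.7 × 0.7) = 73.5, rounded up to 74. Both figures reproduce.

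**Variance of the three contrasts**, relative to a comparison of follow-up scores:

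- follow-up score only: 1
- change from T0: 2(1 − rho)
- T0 as a covariate: 1 − rho²

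Since 2(1 − rho) − (1 − rho²) = (1 − rho)², the covariate analysis has the smaller variance whenever rho is below 1. The change contrast equals the follow-up comparison at rho = 0.5 and is worse below that.

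**The GEE term.** In simulated complete data with T0 as a response and a separate mean for each group and time point, the group-by-time coefficients equalled the between-group differences in mean change exactly, under both independence and exchangeable working correlation.

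**Power for knowledge.** Noncentral t with noncentrality (0.95 / √factor) × √(18/2); 34 degrees of freedom, or 33 with the covariate. For the follow-up t-test the noncentrality is 0.95 × 3 = 2.85, giving 79.1%.

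| assumed rho | follow-up t-test | change contrast | T0 as covariate | gain over t-test | gain over change |
|---|---|---|---|---|---|
| 0.3 | 79.1% | 64.8% | 82.6% | 3.5 | 17.8 |
| 0.4 | 79.1% | 71.5% | 85.5% | 6.4 | 14.0 |
| 0.5 | 79.1% | 79.1% | 89.1% | 10.0 | 10.0 |
| 0.6 | 79.1% | 87.2% | 93.3% | 14.2 | 6.1 |
| 0.7 | 79.1% | 94.7% | 97.2% | 18.1 | 2.5 |

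**Skills.** With d = 1.13, 18 per group and rho = 0.5, the normal approximation gives 92.4% unadjusted and 97.5% adjusted, a gain of 5.1 points.

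**Clustering.** With an assumed intra-cluster correlation of 0.1 and 18/4 = 4.5 staff per home, the design effect is 1 + 3.5 × 0.1 = 1.35. At rho = 0.5 (taken to hold at both the home and the person level, normal approximation), power is 68.9% unadjusted and 80.9% adjusted. The gain is 12.0 points, against 81.3% to 90.8% (9.5 points) on the same approximation without clustering.

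**Chance imbalance.** The SD of the baseline difference between arms is √(2/18) = 0.33 SD with independent staff, and √(2 × 1.35/18) = 0.39 SD at an intra-cluster correlation of 0.1. A t-test of follow-up scores carries rho times this into its estimate: about 0.17 SD at rho = 0.5 with independent staff.

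**The case against.** The article is condensed and says neither which scores the t-test compares nor at which visit. A reader might infer that it fixes a test of raw follow-up scores. The knowledge hypothesis makes that the natural reading, but the text does not state it. If change scores are meant, the change-contrast column applies instead.

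A reader might also infer that the T0 data are thrown away. They are not: the GEE is planned for the same scores, and its interaction removes baseline imbalance and beats the follow-up t-test when rho exceeds 0.5. T0 might also be among the unlisted confounders. The exact equality with change scores was shown for complete data, whereas the plan allows for 30% drop-out.

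Nor do the documents support a flat loss of 10 power points; that figure belongs to an assumed rho of 0.5. Nor would chance imbalance bias the t-test: under randomisation it is part of the sampling error.

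Finally, knowledge is a secondary outcome, sized for 80% power without baseline adjustment, and 36 is a stated minimum. All of this limits the size of the point. It leaves standing that the named t-test cannot use T0 as a covariate, and that nothing in the article says the GEE will.

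**Conclusion.** The point holds as one of efficiency. The independent t-test is stated, cannot adjust for T0, and is less precise than a baseline-adjusted comparison whenever rho is above 0 and below 1. The GEE group-by-time term, if T0 is a repeated response, is less precise than baseline adjustment for any rho below 1.

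For an assumed rho of 0.3 to 0.7, the gain in power for knowledge is about 3.5 to 18 points over a follow-up t-test, and about 18 down to 2.5 points over the change contrast. These figures rest on the article's d = 0.95 taken as a between-group difference in SD units of the follow-up score, 18 analysed per group, and independent staff. Counting clustering lowers the levels; in the example above it leaves a gain of similar size. Baseline imbalance adds noise to the t-test in proportion to rho and does not make it invalid.

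**What to change.** Make the cluster-adjusted model the test of the knowledge hypothesis. Take the week-8 and end-of-protocol scores as outcomes, with group, time, group-by-time and each person's T0 score as a covariate. Report the adjusted group difference at each of the two time points. Drop the independent t-test for knowledge, or label it descriptive.

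Use the same model for skills only if the skills T0 assessment precedes every programme component, including the lecture. Table 1 places it before the skill training, in a separate column from the pre-lecture assessment, so it may come after the lecture. In that case the covariate could absorb part of the effect.

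The cost is about one sentence in the analysis section, with no new data or participants. The small downside is that staff without a T0 score need a simple stated rule, such as mean imputation or a missing-baseline indicator.

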The two-hour lecture will be directed towards HWs and PCWs and cover such topics as PU etiology and assessment, risk factors for the development of PU, PU risk assessments, skin assessments, evidence-based preventive interventions, and the association between daily personal care and PU prevention. The two skill-training sessions will consist of one three-hour training session for HWs and PCWs, and one two-hour training session for HWs only. The contents of the two skill-training sessions have been tailor-made for each type of care staff based on their different duties as noted in the protocol. In the three-hour session, HWs and PCWs will be trained in such skills as turning, positioning, lifting, transferring, the use of pressure-relieving devices, and skin assessments, while the two-hour session for the HW group will cover PU risk assessments using the PU risk form and PU assessments. A return demonstration of the skills will be carried out by the participants to ensure that they are able to perform the skills accurately. As the intensive training course (the lecture and two skill-training sessions) is considered to be in-service training that will enrich their knowledge and skills to improve the quality of care in preventing pressure ulcers, all HWs and PCWs in the experimental group will be required to attend the course. However, their participation in this study will be voluntary. Acting as supervisors of HWs and PCWs, nurses, if available in the experimental group, will required to attend the course so that they will know what HWs and PCWs are learning. Nurses will not be participants in this study. This intensive training course for the four nursing homes in the experimental group will be conducted by the PI and another researcher involved in this study.

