### Study outcomes and measures

The primary outcomes are the incidence and prevalence of pressure ulcers. The secondary outcomes are the care staff’s knowledge and skills on preventing pressure ulcers. These outcomes will pertain to the cluster and individual participant levels.

PU incidence and prevalence: The incidence of PUs will be assessed using the validated PU incidence form [6]. The form will record the numbers, locations, and stages of the PUs that are detected. The common PU sites are numbered from 1 to 36 on a body map. The identification of stages will be adopted from the guidelines of the European Pressure Ulcer Advisory Panel and the National Pressure Ulcer Advisory Panel [7]. The prevalence of PUs will be evaluated using the validated prevalence form [6].

PU prevention knowledge: In this study, the knowledge test, which demonstrated good internal consistency and content validity, [8] will be adopted to assess the care staff’s knowledge of PU. The test has 30 true-false items, with each correct answer allocated a score of one. The range of scores is from 0 to 30, and the total score is 30. A higher score indicates a higher level of knowledge of PU.

PU prevention skill level: The skill checklist, which has good content validity and internal consistency, [8] will be used to assess the care staff’s skills on turning, positioning, transferring, lifting, and use of materials/devices for preventing pressure ulcers. The checklist lists the steps required to demonstrate the five different skills and the rating for the performance of the skill in each step using a 4-point scale: unsatisfactory (1), barely satisfactory (2), satisfactory (3), and very satisfactory (4). A higher total score indicates better skill at preventing PUs.

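### The staff t-test pools health workers and personal care workers and ignores staff type and home; the planned GEE, with staff type as a covariate, should decide hypotheses 2 and 3

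*Protocol article*

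**What the plan says.** The Interventions section describes a course that differs by staff type. The lecture is common to both: "The two-hour lecture will be directed towards HWs and PCWs". The skill training is not: "The two skill-training sessions will consist of one three-hour training session for HWs and PCWs, and one two-hour training session for HWs only". The contents are "tailor-made for each type of care staff based on their different duties as noted in the protocol". Of the HW-only part it says that "the two-hour session for the HW group will cover PU risk assessments using the PU risk form and PU assessments". The course is given only in the four experimental homes; control homes continue usual care.

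Under Study outcomes and measures, staff knowledge and skills are secondary outcomes: "The secondary outcomes are the care staff’s knowledge and skills on preventing pressure ulcers". Knowledge is a 30-item true-false test. The skills checklist covers "skills on turning, positioning, transferring, lifting, and use of materials/devices for preventing pressure ulcers".

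Under Statistical analysis, the between-group comparison is stated as "An independent t-test will be adopted to compare the knowledge and skills of care staff between the two groups". The next sentence adds a GEE for the same two outcomes over time, adjusted for the cluster effect and for confounders that are not named. The article does not say which of the two analyses decides hypotheses 2 and 3.

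The Randomization section assigns eight numbered homes, four to each arm, by random numbers and mentions no stratification. The Sample size section sets no HW:PCW ratio.

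**The concern.** Staff type determines what a participant does at work and, in the experimental arm, how much training that person receives. If HWs and PCWs also differ in average score, two things follow for a two-sample t-test that pools them. The difference between types goes into the error term, which costs power. And any chance difference in the HW share between arms moves the estimated effect. With eight homes and as few as 18 analysed staff per group, such differences will be common. The same test also treats staff from one home as independent, although homes are the randomized units. At stake are the estimates and p-values for hypotheses 2 and 3.

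**Working it through.** **Training hours (Interventions).** HW: 2 + 3 + 2 = 7 h. PCW: 2 + 3 = 5 h. The difference exists only in the experimental arm.

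**Which outcome the extra two hours can reach.** The HW-only session covers risk assessment and ulcer assessment. The checklist scores turning, positioning, transferring, lifting and use of devices, and the Interventions section places all of these in the three-hour session attended by both types. The extra hours therefore do not bear directly on the scored skills. They may bear on knowledge, although the shared lecture also covers assessment topics.

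**The plan's own staff sample size.**
- Inputs: d = 0.95 (knowledge) and 1.13 (skills), 80 % power, significance level 0.05 (taken as two-sided).
- n per group = 2(1.960 + 0.842)²/d². For d = 0.95 this is 17.4, so 18 per group and 36 in total, as stated. For d = 1.13 it is 13 per group, so knowledge drives the size.
- Inflation for 30 % drop-out and 70 % recruitment: 18/(0.7 × 0.7) = 36.7, so 37 per group and 74 in total, as stated.
- Power at 18 per group for d = 0.95: 81.3 % by the normal approximation, 79.1 % by the exact t-test (which needs 18.4, so 19 per group).

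**Precision lost by leaving staff type out.** The article gives neither the HW share p nor the HW–PCW score gap D. Assumed ranges: p = 0.2–0.5 and D = 0.3–1.0 within-type SD. Share of variance explained: R² = p(1−p)D²/(1 + p(1−p)D²). The adjusted effect size is 0.95/√(1−R²). Clustering is ignored here.

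| p | D | R² | Power at 18 per group (normal) | n per group for 80 % |
|---|---|---|---|---|
| 0.2 | 0.3 | 0.014 | 81.9 % | 18 |
| 0.3 | 0.5 | 0.050 | 83.2 % | 17 |
| 0.3 | 0.8 | 0.118 | 85.9 % | 16 |
| 0.5 | 1.0 | 0.200 | 89.0 % | 14 |

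Against 81.3 % unadjusted, the gain is 0.6 to 7.7 points, or about 1–8. The exact t calculation gives the same picture: from 79.1 % to between 79.6 % and 87.2 %.

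**Shift from an unequal staff mix.** Shift = (difference in HW share) × D. Over D = 0.3–1.0, in within-type SD:
- 10 points: 0.03–0.10
- 20 points: 0.06–0.20
- 30 points: 0.09–0.30

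**How often the mix differs.** With 18 independent staff per group, the SD of the difference in HW share is √(2p(1−p)/18): 0.153 at p = 0.3 and 0.167 at p = 0.5. A difference of 20 points or more then has probability 0.20 and 0.24. If the HW share also varies between homes (assumed intra-home correlation 0.05–0.10), simulation gives 0.24–0.32.

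**Home.** With 18/4 = 4.5 analysed staff per home, the design effect is 1 + 3.5 × ICC. For an assumed ICC of 0.01, 0.05 or 0.10 it is 1.035, 1.175 or 1.35, so 18 per group becomes 19, 22 or 25.

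**The case against.** The strongest reply is that the t-test is not the only staff analysis. The same section plans a GEE on knowledge and skills that adjusts for cluster and for possible confounders. Staff type may be among them, and naming covariates is commonly left to the full protocol or SAP. This stands: the missing covariate list is not an error. It does not rescue the t-test, which is a stated method that can take no covariate and no cluster term, and the article does not say that it is subordinate to the GEE.

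Second, hypotheses 2 and 3 concern care staff as a whole and the programme trains both types, so an average over the staff mix is a legitimate target. This also stands. A reader might infer that pooling biases or invalidates the comparison. It does not: imbalance in staff mix arising from randomization is chance variation, not systematic bias.

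Third, a reader might infer that the 7 v 5 hours undermine both staff outcomes. The documents do not support that for skills, since the scored tasks are taught to both types.

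Fourth, a staff-type main effect does not model the difference in training, which exists in one arm only. This is correct. The covariate serves precision and balance; only results shown by staff type speak to the different training.

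Finally, the size rests on assumed inputs and the outcomes are secondary. Both are true and limit the weight of the point.

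**Conclusion.** The point holds as a minor to moderate improvement. The stated t-test leaves out staff type and home, although both are known and relevant. For staff type the cost is about 1–8 power points at 18 staff per group. A 20-point imbalance, which would occur in roughly 20–32 % of allocations for an HW share of 30–50 %, would shift the contrast by 0.06–0.20 SD, small beside the planned 0.95 SD. These figures depend on the assumed HW share, score gap and intra-home correlation; if the two types score alike on average, neither the loss nor the shift arises. Knowledge is the more exposed outcome: it has the smaller planned effect, sets the staff sample size, and is the only one of the two that the HW-only session may touch. The primary pressure ulcer outcomes are unaffected.

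**What to change.** In the Statistical analysis section:
- State that the cluster-adjusted GEE, not the t-test, is the analysis for hypotheses 2 and 3.
- Prespecify staff type (HW or PCW) as a covariate in that model.
- Report the arm differences in knowledge and skills separately for HWs and PCWs as descriptive results, without a claim of power for either subgroup.

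The model is already planned, so the change is in wording plus one model parameter. No new data are needed, because participants in both arms are recruited as HWs or PCWs. Sample size, randomization and intervention stay as they are.

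### Hypothesis 1 is about prevalence at the end of the protocol, but the analysis section lists three tests of it at 0.05, names none as deciding, and aims the cluster-adjusted ones elsewhere

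*Protocol article*

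**What the plan says.** All references are to the protocol article.

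- **Target (Hypotheses).** The first hypothesis fixes one time point: "The experimental group will have a lower incidence and prevalence of PUs than the control group at the end of the implementation of the protocol".
- **Status (Study outcomes and measures).** "The primary outcomes are the incidence and prevalence of pressure ulcers".
- **Timing (Study procedures and Table 1).** Prevalence is surveyed four times: before the training course (T0), then "immediately before the commencement of the implementation of the protocol (T1), at the 8^th^ week (T2), and at the end (T3) of the implementation". T0 and T1 both precede the protocol. These are the labels used for prevalence; the staff outcomes use the same labels for different visits.
- **Tests (Statistical analysis).** First, "A chi-square test will be performed to compare the PU prevalence and PU incidence of residents between the two groups", with no time point and no mention of clustering. Then a GEE compares the groups on the staff outcomes, "as well as in PU status over time, and to examine the groups by the time interaction effect, adjusting for the cluster effect and possible" (the last word refers to confounders).
- **Threshold (Statistical analysis).** One rule covers everything: "Significance will be set at a P value of < =0.05".

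No sentence says which of these results decides the first hypothesis.

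**The concern.** The hypothesis asks a single question: do the arms differ in prevalence at T3? The analysis section offers three answers for the same primary outcome, and they do not all address that question.

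- The chi-square can be applied at T3, but no adjustment for homes is stated for it.
- The GEE is stated to adjust for homes, but its stated targets are a comparison over time and a group-by-time interaction.

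So no listed test is stated to fit both the hypothesis and the cluster design. With none named as deciding, a claim that the programme works could rest on whichever test is significant, and the error rate of that claim would exceed the stated 0.05. The problem would remain for prevalence alone, with every standard error correct. It is therefore separate from having two primary outcomes and from whether the chi-square allows for clustering.

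The point is limited to prevalence. Incidence is recorded over the whole period, so the choice among survey times does not arise for it in the same way.

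**Working it through.** **1. Do the tests share a target?** Write d0, d1, d2, d3 for the difference between arms (log odds) at T0 to T3. Hypothesis 1 concerns d3.

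| Test | Quantity tested | Equal to d3? |
|---|---|---|
| Chi-square, if applied at T3 | d3 | yes, but no cluster adjustment stated |
| Group effect over time, read as an equal-weight average | (d0 + d1 + d2 + d3)/4 | no |
| Overall group-by-time interaction | d1 − d0, d2 − d0, d3 − d0 jointly (3 df) | no |
| T3-versus-T0 contrast from the same model | d3 − d0 | close: randomisation makes the expected d0 zero |

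- If the differences are (0, 0, δ/2, δ), the average is (0 + 0 + δ/2 + δ)/4 = 0.375δ. The two pre-protocol surveys dilute the effect.
- If they are (0, 0, δ, 0), the interaction contrasts are (0, δ, 0). The interaction is real although d3 = 0. This shows that the test does not imply the hypothesis; it is not a forecast of how the effect will run.

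**2. False-positive rate when any test may support the claim.**

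Inputs from the document: four surveys and a threshold of 0.05, taken as two-sided. Assumed, because the document gives no value: an exchangeable correlation ρ between surveys of 0.2, 0.5 or 0.8. There is no cluster inflation, so that each test is exact by itself and only the choice among tests matters.

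Let Z0 to Z3 be the standardised arm differences, jointly normal with mean zero and pairwise correlation ρ.

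- End test: |Z3| > 1.96.
- Average group effect: |Z0 + Z1 + Z2 + Z3| / √(4 + 12ρ) > 1.96.
- Overall interaction: 3-df Wald statistic on Z1 − Z0, Z2 − Z0, Z3 − Z0, against 7.81.
- T3-versus-T0 contrast: |Z3 − Z0| / √(2(1 − ρ)) > 1.96.

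Each test alone rejects in 5.0% of draws, which reproduces the plan's stated level. With one million draws per ρ:

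| At least one significant, no true effect | ρ = 0.2 | ρ = 0.5 | ρ = 0.8 |
|---|---|---|---|
| Two tests: end test, T3-versus-T0 contrast | 8.6% | 9.1% | 9.5% |
| Three tests: end test, average effect, overall interaction | 12.3% | 12.0% | 11.3% |

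Check by hand: with exchangeable correlation the average and the interaction are independent, so those two alone give 1 − 0.95² = 9.75%. Adding the end test must lie between that and 3 × 5% = 15%. Two tests must lie between 5% and 10%. The simulated values obey these limits.

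**3. Direction.** The hypothesis says lower, so only results that favour the programme could support it. Counting only those (and counting the interaction only when the T3 difference favours the programme) gives 4.3% to 4.8% for two tests and 5.6% to 6.2% for three, against 2.5% for a single two-sided 5% test.

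**4. Second check with binary data.** Simulated trials of 8 homes with 98 residents each, 9.5% prevalence throughout, four surveys and a fitted GEE (independence working correlation, resident-level robust errors, 1,500 trials) gave at least one of three tests significant in 15.3% at latent correlation 0.4 and 12.1% at 0.8. The 15.3% is partly not multiplicity: the group effect alone rejected in 8.2% there, because those errors ignore the homes. The figures in step 2 are the cleaner ones.

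**The case against.** **The time point can be inferred.** Read with the Hypotheses section, the chi-square naturally belongs at the end of the protocol. That is fair, and the working uses it so. It does not supply the missing cluster adjustment or say that this test decides.

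**The GEE sentence does not specify an averaged effect or a 3-df test.** This also stands. It may describe one repeated-measures model, and that model yields a T3-versus-T0 contrast that comes close to hypothesis 1. On this reading the excess is smaller, about 9%, but it is not removed, and the text does not name that contrast.

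**An article leaves such detail to an analysis plan.** This is true of working correlation, confounders and coding. But the article does commit itself to particular inferential targets, and these do not match the hypothesis it states. An unadjusted test followed by an adjusted longitudinal model is a common layout; the difficulty is that both carry the same threshold and neither is ranked.

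**Stronger readings that do not hold.**

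- A reader might infer that the same data could both confirm and refute the programme. A non-significant result refutes nothing. The tests can differ in significance mainly because they differ in power and target.
- A reader might also take from simulations with a true effect that the tests will disagree in about half of trials or more. Such rates need an assumed course of effect (for example half the effect at week 8, or one that vanishes while the protocol is still running) and often 80% power for prevalence. The document states neither; its Sample size section powers incidence only.

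**Conclusion.** The point holds in a limited form. For prevalence, a primary outcome, the analysis section lists three tests at one threshold and names none as deciding. The only ones stated to adjust for homes are aimed at something other than the end-of-protocol difference.

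If a claim may rest on any of them, the two-sided false-positive rate is about 9% on the reading most favourable to the plan and about 12% on the three-test reading, instead of 5%. About half of those errors would favour the programme. The range rests on assumed correlations of 0.2 to 0.8 and on each test being otherwise valid. The document does not say that the trial team will choose among results after seeing them; the point is that the text allows it. This should be corrected, but it does not undermine the design.

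**What to change.** In the Statistical analysis section, name one deciding test for prevalence: the 1-df group contrast at the end of the protocol (T3 in the prevalence labels) from the cluster-adjusted GEE. Handle T0 as baseline rather than as an outcome time that enters the group effect. Write out the visit as well as the label, since the labels differ between outcomes. Label the chi-square, the average group effect, the overall group-by-time interaction and the week-8 contrast as supportive, with no claim of effectiveness resting on them.

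The cost is one or two sentences, with no new data, visits or participants. The downside is that a significant chi-square or interaction alone could no longer be reported as confirming hypothesis 1.
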